### Recruitment procedures

We will use a variety of contact methods in our recruitment efforts. Prior to our direct contact with the schools, the prevention officers at the Berlin Senate Department for Education, Youth and Family (SenBJF) will promote the study through a program flyer and an informational e-mail to the target schools. We will gradually contact all primary school secretaries in the selected districts directly by phone to reiterate the offer. Whenever possible, we will request a direct phone call with the school principals to inform them about the program.

In all of these cases, where schools have expressed initial interest, we will arrange in-person recruitment meetings at the schools with principals. We will provide them with a comprehensive presentation of the lesson content, the study itself, and the data assessment, and may use the opportunity to schedule classroom visits.

### Informed consent

Prior to the initial classroom visit, the study team will be available to attend parent meetings and to personally explain all important details of the study. Alternatively, teachers will be instructed to provide parents and children with verbal and written information material about the study. This material includes a comprehensive information sheet, a video, and a flyer summarizing key points for informed consent, provided in English, German, Arabic, Turkish, Russian, and Ukrainian. In the event that students, parents, or teachers require specific clarification, the study coordinators will be available via telephone and email. Prior to the baseline assessment, teachers will collect all consent forms and check them off on a class list for oversight. Before administering the survey on site, the study team will provide a verbal summary of key study information, emphasizing anonymity, the voluntary nature of participation, and the right to withdraw. The team will then review consent forms to begin the assessment. The consent documents feature various levels of consent: Consent to participate in the survey will be a prerequisite for enrollment, while consent to be photographed in the photo challenge and consent to be interviewed after the workshops will be optional.

### Allocation and blinding

After the school principals have given their written consent to participate, schools will be randomly allocated to intervention and control groups by the study coordinator with no role in the analyses of study outcomes. We chose to randomize at the school level to avoid potential contamination effects between intervention and control classes, i.e., through student interaction. During recruitment, blocks of newly enrolled schools (varying in size, with a minimum of 2, stratified by school SES [Berlin school classification index]^37,50^ and number of classes) will be created and allocated sequentially to intervention and control groups in a 1:1 ratio. To remove any researcher involvement, we will use an automated randomization process in R based on a list of random seeds generated prior to school enrollment. Moreover, the data analyses of study outcomes will be conducted by an external statistician unaware of the coding of treatment groups.

School personnel and research staff involved in organizing and or conducting workshops and assessments will inevitably be aware of the treatment condition (i.e., due to visible changes to the classroom environment during the intervention). To mitigate researcher influence, we will enforce standardized and comparable interactions between researchers and students during outcome assessments via meticulously crafted procedural scripts and rigorous training of study personnel. For participant blinding, both control and treatment groups will receive almost identical briefings regarding the study objective, i.e., enhancing the understanding of nicotine use in children, with no mention of the planned comparison of group outcomes.

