### Analytic sample and sample size

We calculated the sample size needed to detect a difference between intervention and control group at 80% power (*α* = 5%) in accordance with the National Institutes of Health recommendations for the analysis of cluster-randomized trials^78^. Consistent with randomization at the school level, the school was treated as the primary clustering unit in a two level structure (school- and student-level observations).

The following estimates of the relevant factors were derived from previous research: Focusing on our continuous primary outcome variable intention, we conservatively assume an intervention effect size of Cohen’s *d* = 0.2^79^. Based on the current literature, the intraclass correlation (ICC) of this psychosocial variable is expected to be lower than that of overtly visible risk behaviors (e.g., smoking) that may be subject to social mimicry^80^. We therefore used an ICC estimate of 0.005, as reported by Siddiqui et. al^81^ for the intention to smoke in 47 schools. Assuming an average cluster size of 60 students with usable data per school, based on an average of 3–4 classes per school with 22 students per class [^77^], our analysis yields a minimum sample size of 10 schools in each study arm (1,200 students). Expecting an attrition rate of up to 20%^52^, we aim to recruit *N* = 1,500 students in at least 26 schools (see Fig. 2: Anticipated participant flow). Because the ICC assumption is subject to uncertainty and higher ICC values would reduce effective power, we will recruit beyond this minimum target if feasible.

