*Proposed mechanisms (mediators).* As specified in our logic model, the main proposed determinants of behavior and mechanisms of change to be underlying the intervention effects on the primary outcome (intention to be vape- and smoke-free) include self-efficacy to be vape- and smoke-free, refusal self-concept, refusal self-efficacy, action planning, descriptive and injunctive norms towards being vape- and smoke-free, and attitudes towards being vape- and smoke-free (direct measure). For behavioral outcomes (i.e., susceptibility, prevalence, and frequency), intention will be modelled as an additional mediator alongside the mentioned psychosocial determinants (e.g., self-efficacy, refusal self-concept, action planning). In addition to the quantitative assessment of mediators via student questionnaires, the proposed mechanisms of change will be explored qualitatively in semi-structured interviews conducted after the core workshop.

*Additional measures.* The baseline assessment will include a number of sociodemographic variables and proposed determinants of vaping and smoking. Among these, age, gender, objective SES, school attachment, parental vaping/smoking, best friend’s vaping/smoking, self-esteem and distress will serve as covariates in the main analysis of intervention effects on the primary outcome. In addition, we will assess SDOH to examine differential intervention efficacy and underlying mechanisms of action by SDOH subgroup. For the purpose of sensitivity analyses, the student questionnaires will also include different attention screeners (e.g., “Please show us that you are reading the questions carefully and mark response option ‘Definitely’; “How much do you agree? ‘I am currently responding to a questionnaire’) and an item to detect careless responding^88^.

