### Analysis

The analyses on intervention effects will be conducted on an intention-to-treat basis, including data from all students based on the groups they were randomly assigned to. The main confirmatory analysis pertains to the group difference between intervention and control group in intention to be vape- and smokefree at the 12-month follow-up (T4), adjusted for baseline (T0). All other analyses, including analyses of secondary behavioral outcomes and additional time points, will be considered secondary or exploratory, and no formal multiplicity adjustment will be applied.

Group differences in secondary behavioral endpoints (i.e., prevalence and frequency measures) will be analyzed across all product categories (e.g., prevalence defined by the use of at least one of the products presented in the questionnaire) as well as individually for each product reported by at least 1% of the sample.

For continuous and dichotomous outcomes, we will use generalized mixed effect regression analyses (i.e., linear regression for the outcome of intention to be vape- and smoke-free; logistic regression for [binary] susceptibility, prevalence measures, current vaping/smoking and regular vaping/smoking). The primary analyses will use a two-level structure, with students at Level 1 nested within schools at Level 2, reflecting the school-level randomization and the role of the school as the primary clustering unit. In regard to count data, we will use Generalized Estimating Equations to conduct zero-inflated negative binomial regressions for count outcomes with many zeros, i.e., the 30-day frequency. We will investigate intervention effects using the criterion of statistical significance (*p* < 0.05) of the regression coefficients for the treatment condition variable (adjusting for prespecified baseline covariates; all measured at T0: intention, age, gender, parental vaping/smoking, best friend’s vaping/smoking, objective socioeconomic status, school attachment, self-esteem and distress). All models will be specified with a maximal random effects structure and progressively simplified as needed to reach convergence.

To handle missing data appropriately, we will conduct a comprehensive analysis of attrition patterns, multiple imputation and sensitivity analyses to check the robustness of our inferences to departures from the underlying assumption of missingness at random.

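### Schools are randomized within strata of school SES index and number of classes, but the stated primary model includes neither stratifier; its standard error is too large to the extent that they are prognostic

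*Protocol article*

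**What the plan says.** Under Allocation and blinding, newly enrolled schools are grouped into blocks "varying in size, with a minimum of 2, stratified by school SES [Berlin school classification index"] and number of classes. The blocks "will be created and allocated sequentially to intervention and control groups in a 1:1 ratio".

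Under Analysis, the confirmatory comparison is intention "at the 12-month follow-up (T4), adjusted for baseline (T0"). On clustering, it says: "The primary analyses will use a two-level structure, with students at Level 1 nested within schools at Level 2". The adjustment set is called prespecified and is listed by name: "intention, age, gender, parental vaping/smoking, best friend’s vaping/smoking, objective socioeconomic status, school attachment, self-esteem and distress". Under Measures, the additional-measures paragraph gives the same set without baseline intention: "age, gender, objective SES, school attachment, parental vaping/smoking, best friend’s vaping/smoking, self-esteem and distress will serve as covariates in the main analysis".

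Neither list contains the school classification index, the number of classes, or a stratum or block term.

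**The concern.** Two items in the article could be mistaken for the missing stratifiers. Objective SES in the covariate lists comes from the student's own baseline questionnaire (Table 4) and is not the administrative school index. The class-level effects planned as sensitivity analyses concern clustering of students within classes, not how many classes a school has.

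Stratified allocation removes chance imbalance between the arms on the stratifiers, so the true sampling variability of the treatment effect no longer includes the variance that they explain. A model that omits them still counts that variance as random school-to-school variation and reports a standard error that is too large. With about 26 randomized units, the school-level variance term matters, and the benefit of stratifying may then not show in the confidence interval or the p-value.

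The article gives some reason to think that school SES is prognostic. Its Introduction links attending a lower-SES school to smoking and vaping initiation, and Table 1 reports that the age of starting varied between schools.

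**Working it through.** **Inputs from Analytic sample and sample size:** d = 0.2 (SD 1), ICC 0.005, 60 students per school, alpha 5%, 80% power, 10 schools per arm (1,200 students), attrition up to 20%, target 1,500 students in at least 26 schools.

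**Assumptions, not in the document:**
- The test is two-sided and done at school level, with a t reference on 2(k − 1) degrees of freedom for k schools per arm.
- R² is the share of between-school variance that the stratifiers explain beyond the listed covariates, set at 0, 25% and 50%.
- An ICC of 0.02 serves as the less favorable case.
- The arms are balanced on the stratifiers, and the stratifiers use 2 degrees of freedom.

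**1. The plan's own figure.** The plan seeks the sample "needed to detect a difference between intervention and control group at 80% power". Individual randomization needs 393 per arm. The design effect is 1 + 59 × 0.005 = 1.295, giving 393 × 1.295 = 509 per arm, or 509/60 = 8.5 schools. With the t reference, 9 schools per arm give 77.4% power and 10 give 82.1%, so 10 per arm (1,200 students) is reproduced. Then 1,200/0.8 = 1,500, and 1,500/60 = 25 schools, or 26 for equal arms.

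**2. Students analyzed per school.** 1,500 × 0.8/26 = 46.

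**3. Formulas.** The variance of a school mean is
- without stratifiers: V₀ = ICC + (1 − ICC)/46
- with stratifiers: V₁ = ICC × (1 − R²) + (1 − ICC)/46

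The SE of the treatment effect is √(2V/13), and the SE ratio is √(V₁/V₀).

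**4. ICC 0.005.**
- V₀ = 0.005 + 0.995/46 = 0.02663; SE = 0.0640; power 85.0% on 24 df.
- R² = 0: ratio 1.000; power 84.7% on 22 df.
- R² = 25%: V₁ = 0.02538; ratio 0.976; power 86.4%.
- R² = 50%: V₁ = 0.02413; ratio 0.952; power 88.0%.

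**5. ICC 0.02.**
- V₀ = 0.02 + 0.98/46 = 0.04130; SE = 0.0797; power 67.3%.
- R² = 0: ratio 1.000; power 66.9%.
- R² = 25%: V₁ = 0.03630; ratio 0.937; power 72.5%.
- R² = 50%: V₁ = 0.03130; ratio 0.871; power 78.6%.

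**6. Actual size of the nominal 5% test without stratifiers.** This is the two-sided tail probability of t on 24 df beyond 2.064 divided by the SE ratio. For R² = 25% and 50% it is about 4.5% and 4.0% at ICC 0.005, and about 3.8% and 2.6% at ICC 0.02. At R² = 0 it is 5%.

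**7. Simulation check** (26 schools, 46 students each, four strata, 6,000 runs per setting, R² = 50%):

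| ICC | Model | Mean SE | Type I error | Power |
|---|---|---|---|---|
| 0.005 | without stratifiers | 0.0634 | 4.3% | 86.0% |
| 0.005 | with stratifiers | 0.0600 | 5.2% | 88.1% |
| 0.02 | without stratifiers | 0.0797 | 2.3% | 68.7% |
| 0.02 | with stratifiers | 0.0685 | 4.9% | 78.6% |

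The simulation agrees with the formulas in direction and approximate size. It fitted four strata as dummies (3 df) rather than 2 df.

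**The case against.** **The list may not be exhaustive.** It is described as covariates measured at T0, and the school index and class count are administrative design variables. The article refers to its pre-registration for further analysis details, and that file is not shown. This lowers certainty about what will be fitted. It does not remove the point, because the article itself names the adjustment set for its one confirmatory test. If the pre-registration adds the stratifiers, the article states the model incompletely.

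**The loss is conditional.** It arises only from variance that the stratifiers explain beyond nine covariates, which include baseline intention and student SES. No figure for this is given. Recruiting only in six high-burden districts may narrow the range of the index, and nothing in the article links number of classes to intention. All of this stands, and it is why R² = 0 belongs in the range.

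**The effect is small at the planned ICC.** This stands too. The larger figures need an ICC of 0.02, which is not in the document, although the sample size section admits that the ICC is uncertain and that a higher value would cost power.

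**Balance may be incomplete.** With small blocks, two stratifiers and about 26 schools, the true test size would lie closer to 5% than calculated here.

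**Stronger readings that the article does not support.** A reader might infer that omitting the stratifiers biases the treatment effect or produces false positives. It does neither: the error is toward caution. A reader might also infer that the estimator itself becomes less precise. Under balance the point estimate is essentially unchanged, and it is the reported standard error that is too large. Nor does it follow that every treatment-effect model must carry the stratum terms. The linear-model argument does not transfer directly to rare-event logistic or zero-inflated models, and Table 1 suggests that regular use involves only one or two students per grade cohort.

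**Conclusion.** The point holds in a limited form. The design and the stated primary model do not match: schools are stratified on two school-level factors, and neither is in the adjustment set. The consequence is a conservative confirmatory test, to the extent that the stratifiers carry prognostic information beyond the listed covariates.

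At the protocol's own ICC the expected gain from correcting it is modest, at most about three points of power for R² up to 50%. It reaches about 11 points only if the ICC is nearer 0.02 and R² is 50%. If R² is zero, correcting it costs 0.3 to 0.4 points. The comparison favors including the stratifiers, but the trial's validity does not depend on it.

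These sizes rest on the assumed R², the assumed higher ICC, balanced arms and a school-level t reference.

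**What to change.** In the Analysis section, add the school classification index and number of classes as school-level fixed effects in the primary linear mixed model. Code them sparingly, for example one term each (about 2 of the 24 school-level degrees of freedom), and do not use a dummy for every randomization block. In secondary models, include them only where event counts allow, and say so. If the pre-registration already specifies them, align the article's covariate lists with it.

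The school index and class count are needed for randomization, so no new data collection is required. The change is one sentence, and it should be made before outcome data are analyzed by arm, because a later addition to a list described as prespecified would look post hoc.

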### Intervention and comparator

The intervention is taught during school hours by a tandem of research assistants with an expertise in human medicine, health sciences or psychology (i.e., (under-)graduate students or professionals), whose members alternate in leading the intervention (i.e., the psychologist discusses mental health and addiction; the medical practitioner explains biological processes).

The intervention program comprises three basic components that are conducted at three-month intervals in the course of one school year:A 180-min *Core Workshop* delivered by the study team that can be taught in two separate sessions. The primary objective of this workshop is to educate students about the consequences of vaping and smoking, enabling them to identify and resist unfavorable social influences and to cultivate positive social norms. Additionally, the workshop aims to facilitate the acquisition of critical thinking about the influences of advertising and social media.A 90-min mid-term *Booster Session*, which serves to refresh and deepen the content of the core workshop. The booster consists of two parts: approximately 45 min taught by the class teacher and 45 min taught by the study team. The teacher-led part consists primarily of the students creating a poster advertisement for a vape- and smoke-free life, a task that can be implemented with minimal teacher preparation and no additional training. Materials are provided to schools in advance, and the task serves as preparation for the subsequent visit by the study team.A 90-min, more comprehensive *Life Skills Training* module, led by the study team, focusing on problem solving and managing uncomfortable emotions, such as stress and anxiety.

An overview of intervention content, employed BCTs and targeted theoretical determinants is provided in Table 3.

**Table 3 Tab3:** Overview of workshop modules, key content, BCTs and targeted theoretical determinant of vaping and smoking behavior.

Workshop	Content/key message	Key BCTs^a^	Key change objective in our assessment model^a^
Common techniques and objectives in Core Workshop and Booster		Information about antecedents [4.2], Information about health consequences [5.1], Salience of consequences [5.2], Information about social and environmental consequences [5.3], Credible source [9.1], Social reward [10.4], Framing/reframing [13.2], (Autonomy-supportive interaction style, not in taxonomy [^65^])	Instrumental/Experiential attitude Intention Refusal self-concept/ Self-efficacy to refuse/ Self-efficacy to be vape- and smoke-free Descriptive/Injunctive norm
Core Workshop Part I	*Future aspirations:* Sharing future goals; instructors frame vape- and smoke-free living as an important decision for the students’ future. Health: Expert quiz covering cardiovascular system functions; harmful ingredients and health consequences; effects on appearance (partly adapted from [^68^), general fitness and athletic performance; smoking experiment demonstrating tar deposition in the lungs [^69^]	Comparative imagining of future outcomes [9.3], Imaginary reward [16.2]	
	*Social influences and refusal training:* Sharing experiences with peer pressure; strategies to refuse smoking; action planning using a volitional help sheet (adapted from [^70^])]; model dialogue by the instructors; role-play exercise of saying ‘no’	Problem solving [1.2], Action planning [1.4], Commitment [1.9], Instruction on how to perform a behavior [4.1], Demonstration of behavior [6.1], Behavioral practice/rehearsal [8.1], Verbal persuasion about capability [15.1], Prompts/cues [7.1]	Action planning
Core Workshop Part II	*Addiction and well-being:* Understanding addiction development including the role of social influences; implications for mental well-being. *Monetary costs:* Exploring the financial impact of smoking versus being vape- and smoke-free. *Marketing and Lobbyism:* Examining tobacco industry influence on tobacco control-policies; manipulative marketing strategies; ethics in advertising	Information about emotional consequences [5.6], Information about health consequences [5.1], Information about others’ approval [6.3], Pros and cons [9.2], Imaginary reward [16.2]	
	*Living vape- and smoke-free:* Normative feedback on the high percentage of vape- and smoke-free students in the class (adapted from [^71^]); Danish campaign presentation: “cool without smoke” [^72^] ; video message from German actor introducing the “photo challenge”: taking pictures for an advertising campaign demonstrating the appeal of a vape- and smoke-free life	Feedback on behavior [2.2], Information about others’ approval [6.3], Social comparison [6.2], Identification of self as role model [13.1], Identity associated with changed behavior [13.5], Reward incompatible behavior [14.7], Prompts/cues [7.1]	
Booster Sessions (90 min led by class teacher, 45 min led by study team)	*Recap and sharing:* Reflection on the content of previous workshops; sharing experiences with refusing smoking and recapitulating strategies using the volitional helpsheet (adapted from [^70^]). *Poster creation and presentation:* Creating and presenting advertisement posters around the theme of being vape- and smoke-free, using photos taken in the Core Workshop Part II	Problem solving [1.2], Social support [3.1], Feedback on behavior [2.2], Social comparison [6.2], Identification of self as role model [13.1], Identity associated with changed behavior [13.5], Reward incompatible behavior [14.7], Action planning [1.4], Commitment [1.9]	Action planning
Life Skills Training^a^	*Resources:* Recognizing personal resources and committing to daily self-care; “Emergency-Powercard” with 24/7 support hotlines. *Coping and problem solving:* Action planning for challenging situations and unpleasant emotions; breathing exercise (adapted from [^73^]	Reduce negative emotions [11.2], Problem solving [1.2], Instruction on how to perform a behavior [4.1], Demonstration of behavior [6.1], Behavioral practice/rehearsal [8.1], Action planning [1.4], Commitment [1.9], Prompts/cues [7.1]	Coping with stress Distress Action planning

^a^The objective of the life skills training is to cultivate adaptive strategies for coping with stress and problem solving. The interventionists do not mention smoking and vaping; therefore, in the corresponding row of the table, we provide codes for BCTs aimed at fostering adaptive coping with stress and problem solving. With regard to the intervention’s overall goal of students being vape-and smoke-free, the entire session can be coded as the BCT “Reduce negative emotions [11.2]”.

